## Abstract

**Introduction:**

Children with Cerebral Palsy (CP) encounter substantial nutritional challenges that impair their health and quality of life. Despite the importance of nutrition in managing CP and the recognition of physiological, behavioral, and social causes of malnutrition, research on the effectiveness of individualized nutritional interventions developed and supported by multidisciplinary teams is scarce.

**Aim:**

The study will evaluate the impact of an individualized nutritional intervention developed and supported by a multidisciplinary team on the anthropometric outcomes and overall health of children with CP.

**Methods:**

A single-center, randomized controlled trial, conducted at the Medical University of Varna, Bulgaria, will enroll 100 children aged 2–12 years and diagnosed with CP. Participants will be randomly assigned to either an intervention group, receiving comprehensive structured dietary assessment and individualized nutrition plan developed by a multidisciplinary team of experts, or to a standard care group. Outcomes assessed will focus on anthropometric measures of nutritional status, but also include health outcomes, child development and clinical assessments, and quality of life indicators.

**Ethics:**

Ethical approval for this study has been obtained from the Medical Ethics Committee at the Medical University of Varna (Protocol No. 134 dated 20.07.2023).

**Conclusion:**

This study will assess the benefits of a multidisciplinary, individualized nutritional intervention for children with CP. The findings will have implications for clinical guidelines and interventions aiming to improve their care and quality of life.

## Abbreviations

BMIAZBody Mass Index for Age Z-scoreCPCerebral PalsyDP-3Developmental Profile-3EDACSEating and Drinking Ability Classification SystemESPGHANEuropean Society for Paediatric Gastroenterology, Hepatology, and NutritionFFQFood Frequency QuestionnaireGMFCSGross Motor Function Classification SystemHAZHeight for Age Z-scoreITTIntention-To-TreatMUACAZMid-Upper Arm Circumference for Age Z-scorePPPer-ProtocolPEDI-EATPediatric Evaluation of Disability Inventory - Eating ModuleQoLQuality of LifeRCTRandomized Controlled TrialSFTAZSkinfold Thickness for Age Z-scoreSPIRITStandard Protocol Items: Recommendations for Interventional TrialsWAZWeight for Age Z-scoreWHOWorld Health Organization

## Introduction

1

Cerebral Palsy (CP) encompasses a group of permanent movement and posture disorders, leading to activity limitations due to non-progressive disturbances in the developing fetal or infant brain (Rosenbaum et al., 2007). As the most prevalent physical disability in childhood, CP affects approximately 1.6–3.4 per 1000 live births globally [1].

Children with CP encounter numerous health challenges, including malnutrition, which aggravates their physical limitations and negatively impacts their own quality of life (QoL) and that of their families [2]. Malnutrition in CP results from feeding difficulties, inadequate dietary intake, elevated energy expenditure, and malabsorption, highlighting the need for tailored nutritional interventions [3].

While nutritional interventions are pivotal for enhancing nutrient intake, growth, functional abilities, and thus QoL, empirical evidence supporting their effectiveness in CP is sparse. High-quality, randomized controlled trials (RCTs) are imperative to inform clinical practices [4].

Current literature reveals a significant knowledge gap in designing and implementing effective, practical, and family-friendly comprehensive nutritional interventions for children with CP. This RCT aims to bridge this gap by evaluating a nutritional intervention's efficacy in promoting growth and QoL, and in reducing bedridden days among children with CP. The ultimate objective is to establish an evidence-based framework for nutritional interventions within clinical care for children with CP, potentially enhancing their health outcomes and QoL.

In many countries, including Bulgaria, nutritional assessment and management are not standardized components of clinical care. This study presents an ethical opportunity to examine if such practices can effectively improve patient well-being, beyond existing clinical and family-led care, particularly in contexts like Bulgaria. Amidst the high costs of medical care—in terms of money, time, and emotional toll—this research advocates for evidence-based healthcare practices and standards.

## Objectives

2

### Primary objective

2.1

To evaluate the effect of an individualized nutritional intervention based on multidisciplinary assessment on the nutritional status of children with CP over a six-month period.

### Secondary objectives

2.2

●***Healthcare*** utilization outcomes: To assess the nutritional intervention's efficacy in decreasing the number of bedridden days. Optimal nutrition can fortify physical capacities, potentially leading to more active days [5]. Assessing the effect of the intervention at this level could inform health care policy in Bulgaria and abroad.●Developmental outcomes: To investigate the potential cognitive enhancements associated with the nutritional intervention. Recent research suggests that nutrition has downstream effects on cognitive function [6]. It is unclear, however, whether these effects can be observed as a result of a brief intervention.●Quality of Life outcomes: To determine the impact of the intervention on enhancing the overall quality of life for children with CP. Improvements in nutrition and physical health can be subsequently reflected in increased well-being and life satisfaction, as captured by established assessment tools [7].

## Design and methods

3

### Study setting

3.1

The study will be a prospective, single-center, RCT conducted at the Medical University of Varna. This protocol adheres to the Standard Protocol Items: Recommendations for Interventional Trials (SPIRIT) 2013 [8] statement to prevent study design-related bias.

### Participants and recruitment

3.2

The target population is 2- to 12-year-old children diagnosed with CP. Participant recruitment will adhere to clearly defined inclusion and exclusion criteria (see Eligibility).

The research team will collaborate with Karin Dom Foundation, a national leader in services for children with disabilities, residential centers, and other relevant organizations to identify potential participants. After an initial phone screening, a psychologist???? will conduct an intake interview with guardians to assess child eligibility. The families of eligible children will be thoroughly briefed on the RCT's aims, benefits, and risks. Written consent from parents or guardians will be required for participation. All personal information will be kept confidential and the data will be anonymized for analysis.

### Eligibility

3.3

#### Inclusion criteria

3.3.1

Children aged between 2 and 12 years who have been diagnosed with cerebral palsy by a qualified neurologist will be eligible for the study. The diagnosis of CP can refer to spastic, dyskinetic, ataxic, or mixed CP. Only children of families who intend to continue to reside in the catchment area for the duration of the study will be included.

#### Exclusion criteria

3.3.2

Children will be excluded for the following reasons: 1) acute medical conditions or severe infections in the 10 days prior to the family being contacted; 2) genetic syndromes affecting nutritional status like Silver Russel or Down syndrome; 3) participation in dietary interventions within the last three months; and 4) guardians do not fully understand the study's terms or don't speak Bulgarian.

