### Study measurements and outcomes

3.4

This trial has comprehensive baseline and final measurements of all trial outcomes (Table 1). Additionally, at baseline we will collect demographic details about the child (age, gender, ethnicity, and socio-economic status of their immediate family), their medical history (focusing on CP diagnosis, the severity of neurological impairments, and any other prevalent medical conditions including comorbid disorders) and their primary caregiver (relationship to the child, educational background, and involvement in the child's daily care).

**Table 1 tbl1:** Overview of instruments and timepoints.

Questionnaire/Activity	Study start	During study					
	Visit 1 (0 month)	Follow up 1 month (±5 days)	Follow up 2 months (±5 days)	Follow up 3 months (±5 days)	Follow up 4 months (±5 days)	Follow up 5 months (±5 days)	Visit 2 (6 months ± 15 days)
Information for parents	✓						
Signed Informed consent	✓						
Demographic questionnaire	✓						
Collected Health record data	✓						✓
Psychodiagnostic test DP-3	✓						✓
Nutrition questionnaire by Speech therapist	✓						✓
EDACS or mini EDACS	✓						✓
Pedi-EAT_	✓						✓
3-day Food diary	✓						✓
Nutrition Questionnaire about feeding problems and food preferences	✓						✓
Quality of life questionnaire	✓						✓
Anthropometry	✓						✓
Biochemical tests	✓						✓
Follow up interview after Visit 1 (e-mail)				✓			
Follow up interview after Visit 1 (GSM)		✓	✓		✓	✓	

Importantly, child assessments will be conducted by a multidisciplinary team consisting of nutritionists, speech therapists, psychologists, pediatric gastroenterologists. A nutritionist will use the findings from the assessment and collaborate with the team in developing the individualized nutritional plans for children in the intervention arm (see below).

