During intake, further assessment of the inclusion and exclusion criteria will occur, alongside evaluation for the presence of comorbid disorders. Family and Child Characteristics will be collected, including:1Demographic Details: Age, gender, ethnicity, and socio-economic status of the child and their immediate family2Medical Profile**:** A detailed recording of the child's medical history, focusing on CP diagnosis, the severity of neurological impairments, and any other prevalent medical conditions including comorbid disorders.3Acute medical conditions Profile: Additional data on the number type and frequency of acute medical issues in the last 6 months will be collected4Caregiver's Profile: Information on the primary caregiver's relationship to the child, their educational background, and their involvement in the child's daily care.5Developmental assessment will be based on the Developmental Profile-3 test (DP-3) ([9], which evaluates development from birth to age 12 across five functional domains: Physical Development, Adaptive Behavior, Social-Emotional Development, Cognitive Development, and Communication. The DP-3 is conducted in the form of an interview with the child's parents or caregivers, and the instrument is administered by certified psychologists. The developmental assessment scale DP-3 is standardized for Bulgaria, and the obtained quantitative results allow for a comparative analysis with the results of a normative sample by age and gender. Additionally, it enables reporting differences in each of the functional areas of development before and after the application of a given intervention.6Quality of Life and Needs Assessment:●Needs Assessment**:** Structured interviews and surveys to explore the effects of the child's neurological challenges on family dynamics and support systems.●Quality of Life Measure: Employing established and validated tools, such as the Beach Center Family Quality of Life Scale, this assessment method systematically gauges families' perceptions across critical dimensions including Family Interaction, Parenting, Emotional Well-being, Physical/Material Well-being, and Disability-Related Support.7Dysphagia Evaluation:●Eating Abilities Analysis: Conducted by a speech therapist using the Pediatric Evaluation of Disability Inventory - Eating Module (PEDI-EAT) to assess speech, oral motor function, communication skills, and feeding and swallowing abilities.●Direct Feeding Assessment: In-depth evaluation through clinical examinations, caregiver interviews, and mealtime observations using the Eating and Drinking Ability Classification System (EDACS) and mini-EDACS.●Direct Swallowing Examination**:** Clinical evaluations and oral motor assessments to ensure safety during eating and drinking.8Nutritional Status Assessment: Conducted by a nutritionist, including measurements of height, weight, skinfold thickness, and mid-upper arm circumference, with results plotted against WHO standards and CP-specific growth charts. Dietary intake will be assessed using a 3-day food diary, a Food Frequency Questionnaire (FFQ), and evaluations of food and texture preferences, as well as gastrointestinal issues such as constipation, dysphagia, and gastroesophageal reflux.

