#### Evaluating nutritional progress

3.8.1

The study will assess the nutritional status of participants using key physical measurements, including Body Mass Index for Age Z-score (BMIAZ) when it is possible to obtain a reliable height or length measurement, Weight for Age Z-score (WAZ), Height for Age Z-score (HAZ) or Knee height for Age Z-score (if feasible), Triceps and subscapular Skinfold Thickness for Age Z-score (SFTAZ), and Mid-Upper Arm Circumference for Age Z-score (MUACAZ). Z-scores will be calculated based on WHO growth charts or CDC-charts for skin folds. Weight will be compared with CP-specific growth charts. The transformation in nutritional status is further delineated by alterations in energy intake, captured through detailed analysis of a prospective 3-day food diary. Complementing these measurements, biochemical assessments provide insights into the iron status (ferritin and Hb values), 25-OH-vitamin D levels, and vitamin B12 concentrations, offering a comprehensive view of the nutritional intervention's impact.

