## Planned analyses

4

The outcomes of the intervention will be assessed using both Intention-to-Treat (ITT) and Per-Protocol (PP) approaches. In the ITT approach, analyses include all study participants who were randomized to either of the study arms. In the PP approach, the analyses are restricted to participants who adhere to the protocol. We will not perform any imputation for missing data. Typically, the ITT method is favored for trials aiming to demonstrate superiority or non-equivalence (such as our study), PP approach is more suitable for trials assessing equivalence or non-inferiority Ahn et al., [15]. Nonetheless, it is advisable to execute both methods of analysis and compare their outcomes to identify any notable discrepancies. Employing both the ITT and PP strategies offers a fuller understanding of the effects of the treatment and enhances the credibility of the trial findings. In the case of the ITT analysis, we will focus on Weight for age Z-score (WAZ) (based on WHO standards 2006–2007) [16]. As WAZ is a standardized score for an individual given population norms, we anticipate the intervention to produce change at the tails of the distribution (for children outside the normal range) rather than the center (children in the normal range). This suggests that, in the intervention group, the baseline WAZpre variable may have a cubic relationship with the outcome WAZpost variable (Fig. 2).

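### The 10-day acute-illness exclusion is counted back from contact with the family, not from the Visit 1 measurements, so a child who falls ill in between is eligible and can be measured while ill (minor)

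*Protocol article*

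**What the plan says.** Section 3.3.2 (Exclusion criteria) lists as its first reason for exclusion "acute medical conditions or severe infections in the 10 days prior to the family being contacted". The reference day is the day of contact.

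Section 3.2 (Participants and recruitment) places further steps after that day: "After an initial phone screening, a psychologist???? will conduct an intake interview with guardians to assess child eligibility". No maximum interval between contact, interview and Visit 1 is given.

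Table 1 in section 3.4 puts anthropometry, biochemical tests and the 3-day food diary at Visit 1 and again at Visit 2, with no anthropometry in between.

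Section 3.4 also says: "During intake, further assessment of the inclusion and exclusion criteria will occur". In the same list it adds, on illness history: "Additional data on the number type and frequency of acute medical issues in the last 6 months will be collected". Neither statement moves the 10-day window to the measurement day, and no use of the illness history for timing the measurements is stated.

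The values at stake are used in three places:
- In the ITT analysis (section 4), "we will focus on Weight for age Z-score (WAZ"), with the baseline value as covariate in both models.
- Section 3.8.1 takes biochemical outcomes including "iron status (ferritin and Hb values"), and energy intake from the diary.
- Sections 3.4 and 3.6 use the baseline assessment to write each intervention child's plan, and section 3.6 judges adherence at six months mainly by improvement in the diary.

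**The concern.** An illness-free window serves the trial best when it protects a measurement. Here it ends before the measurement is made. A child who was well for 10 days before the call and then develops an infection satisfies the criterion as written. That child's weight, ferritin and diary intake at Visit 1 may reflect the illness and not the usual state. The reverse also occurs: an acute condition eight days before the call triggers the exclusion even if the child is well by Visit 1.

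Three uses of the baseline are exposed. The WAZ model rests on a single baseline weight, so a transient loss is not averaged out. The effect is expected in the tails of WAZ, and the most complex candidate model contains the cube of baseline WAZ, which magnifies error for low-weight children. An illness diary can feed into the nutrition plan, and it can also make a child look adherent at six months merely because intake has recovered. That matters for the per-protocol set, which is limited to participants who adhere. Ferritin rises with infection, so a baseline value taken during illness can hide iron deficiency; section 3.8.1 names no inflammation marker alongside it.

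**Working it through.** **Timing, read side by side**

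| Step | Section | Illness condition attached |
|---|---|---|
| Family contacted | 3.3.2 | None of the named conditions in the preceding 10 days |
| Phone screening, then intake interview | 3.2 | None of its own |
| Re-check of criteria at intake | 3.4 | Same criterion, still dated from contact |
| Visit 1 weight, blood tests, diary | 3.4, Table 1 | None |

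Repeating a criterion dated from contact gives the same answer at intake as on the phone. Illness that begins after contact lies outside the window at both checks.

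**Size for WAZ (illustration)**

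The documents give neither the illness frequency nor its effect on weight. Assumptions:
- A 15 kg child loses 3–5% of body weight: 0.45–0.75 kg.
- One WAZ unit is about 2 kg at that weight, so the transient shift is d = 0.225–0.375 WAZ.
- The share ill at the visit is p = 5–15%.
- The six-month residual SD is 0.4 WAZ (variance 0.16).

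Added variance is p(1 − p)d². It is carried in full into the residual, which takes the slope on baseline WAZ as about 1.

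- Low: 0.05 × 0.95 × 0.225² = 0.0024; 0.0024 / 0.16 = 1.5%.
- Middle: 0.10 × 0.90 × 0.30² = 0.0081; 0.0081 / 0.16 = 5.1%.
- High: 0.15 × 0.85 × 0.375² = 0.0179; 0.0179 / 0.16 = 11.2%.

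**Effect on power**

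Reference: one coefficient tested in model (1), two predictors, N = 100, f2 = 0.075, noncentral F with λ = f2 × N = 7.5 and 97 residual degrees of freedom. With two-sided alpha 0.05 (assumed; the text gives no alpha), power is 0.774. Section 4.1 states 0.8. That difference is a separate matter and does not bear on this point.

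Inflating the residual variance divides f2 by the same factor:

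| Case | f2 after inflation | Power |
|---|---|---|
| No illness noise | 0.0750 | 0.774 |
| Low | 0.075 / 1.015 = 0.0739 | 0.768 |
| Middle | 0.075 / 1.051 = 0.0714 | 0.753 |
| High | 0.075 / 1.112 = 0.0674 | 0.729 |

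The loss is about 0.6, 2.0 and 4.4 percentage points. The high case needs 15% of children ill at Visit 1, all with the largest assumed weight loss.

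**The cubic term**

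A shift from −3.0 to −3.3 in baseline WAZ moves the cube from −27.0 to −35.9. Baseline error therefore weighs more if the most complex model is selected. The documents do not allow that to be turned into a power figure.

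**Ferritin and diary**

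The documents contain nothing from which a size could be calculated.

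**The case against.** The strongest reply is that the re-check already deals with this. Section 3.4 lists the nutritional measurements under the same intake at which eligibility is re-assessed, and staff will be asking about acute illness in the last six months. A sensible team would notice a sick child and postpone. This stands in part: the occasion to catch illness exists, and the gap between contact and Visit 1 may be short. But the rule that staff would be applying still names the contact date, so the written criterion does not tell them to act.

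The contact date may also serve another purpose, such as not approaching families during a crisis. No such purpose is stated, and it would not protect the measurements.

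A reader might infer three stronger points that the documents do not support.

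- *Eligible children are lost for good.* Nothing says that the exclusion is permanent or that a family cannot be contacted again, and a condensed article may leave re-screening to the full protocol.
- *Visit 2 is defective because no illness condition applies there.* An exclusion criterion governs entry, not follow-up. A deferral rule for follow-up visits is detail that an article commonly leaves out, and the ±15-day window leaves room for deferral. Infections are also a trial outcome (section 3.8.2) and may differ by arm, so moving visits because of illness would act on a post-randomization event.
- *The treatment comparison is biased.* Illness at baseline arises before treatment can act. Under randomization it falls on both arms alike in expectation, and transient recovery occurs in both.

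**Conclusion.** The point holds as a minor defect in stated text. The illness window ends at contact, the measurements come later, and the intake re-check does not close the gap. The consequence is mainly non-differential noise in baseline WAZ, plus possible distortion of baseline ferritin and of the diary used for the plan and the adherence judgement.

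For WAZ the effect is probably small: a loss of about 0.6 to 4.4 percentage points of power, with about 2 in the middle case. That range rests wholly on the assumed illness frequency, weight loss, WAZ scale and residual SD, and on the assumed alpha. How often the situation arises depends on the interval from contact to Visit 1, which is not stated. The point does not extend to bias in the treatment effect, to permanent loss of eligible children, or to a fault at Visit 2.

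**What to change.** Reword exclusion criterion 1 so that the 10-day window runs back from the Visit 1 measurements (anthropometry, blood sampling and the diary days). State in section 3.4 that the re-check at intake applies the criterion on that basis. For an affected child, defer Visit 1 and randomization until the condition is met, and do not exclude the child.

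The cost is a change of wording in two places and some delayed baseline visits. Because the deferral comes before randomization, it cannot differ by arm and loses no outcome data.

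No deferral rule is requested for Visit 2. At most, record whether the child is acutely ill at that visit, keep the measurement, and use the record in a sensitivity analysis. Such an analysis conditions on a post-randomization event and should be read with that in mind.
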